### Statistical analysis

2.6

Statistical analyses will be implemented by SPSS 17.0 and Microsoft Excel 2007 software. Data will be represented as mean ± standard deviation (SD). A *t*-test will be performed to compare the changes in measures within groups. Statistical significance will be considered at *P* < .05.

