### Research object

2.1

We aim to compare the efficacy including survival rate, sensitivity, specificity and accuracy of in patients divided into CTA group, mimics group and CTA + mimics group in the repair of head and neck soft tissue defects with anterolateral thigh flap.

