### Interventions

2.4

Patients will be randomly divided into CTA group (n = 20), mimics group (n = 20) and CTA + mimics group (n = 20) according to the numerical table. Patients in the CTA group will receive CTA examination of lower extremities. Patients in mimics group will receive digital technology in the positioning of perforator. Patients in CTA + mimics group will receive CTA + digital technology. All the patients will receive the flap cutting and the flap making; the doctor will determine the perforation branch of the flap with 3-D visual positioning, measure the preoperative indicators intraoperatively and complete the wound repair. Finally, the survival rate, sensitivity, specificity and accuracy of the flap will be measured.

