### Measurement of outcomes

2.5

Vascular anatomy and preoperative design results of the anterolateral thigh flap will be recorded, and intraoperative and preoperative comparisons will be analyzed to explore the clinical efficacy of postoperative patients. After the completion of image digitization, 2 physicians who have been working on the anterolateral thigh flap for more than 4 years read the images in a double-blind way to evaluate whether the location, shape, and scope of the lesion of the patient has invasion or metastasis. When opinions will be different, they read the images together and agreed. Consistency analysis by CTA joint digital technology, digital technology and CTA in the defects of head and neck cancer patients in the orientation of value, when the CTA inspection found perforators preoperative and intraoperative confirmed existence is judged to be (+), when the digital technology can be worn for successful reconstruction is judged to be (+), either in the joint inspection tests to determine the (+), finally to the 3 ways to wear the positioning performance comparison.

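### The only test named, a t-test of within-group change, fits neither the three-group aim nor the proportions it is meant to compare

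*Protocol article*

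**What the plan says.** - **Aim (section 2.1, Research object).** "We aim to compare the efficacy including survival rate, sensitivity, specificity and accuracy of in patients divided into CTA group, mimics group" and a combined group. This is a comparison between groups.
- **Allocation and outcomes (section 2.4, Interventions).** Sixty patients are randomised 20:20:20. The outcomes come at the end: "Finally, the survival rate, sensitivity, specificity and accuracy of the flap will be measured".
- **Outcome assessment (section 2.5, Measurement of outcomes).** Each localisation is scored as positive or not, both for CTA and for the digital technology. The section mentions a consistency analysis and ends with a comparison of the three methods: "finally to the 3 ways to wear the positioning performance comparison". It also says that "intraoperative and preoperative comparisons will be analyzed to explore the clinical efficacy of postoperative patients". No test is attached to any of these.
- **Analysis (section 2.6, Statistical analysis).** Data are summarised as mean and SD. A t-test "will be performed to compare the changes in measures within groups", and significance is set at P < .05. No other inferential test is named anywhere in the article. Section 2.2, item 7, names software for the preoperative and intraoperative measurements but no test.

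**The concern.** The article does more than leave the between-group test to a fuller document. It names a test and directs it at a contrast other than the one in its aim. A within-group test asks whether a measure moved inside one arm. It cannot say whether one localisation method is better than another, which is the reason for randomising.

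The type of data does not match either. Mean, SD and a t-test belong to continuous measurements, whereas the four outcomes in the aim are proportions built from yes/no results. An analyst who followed section 2.6 literally would have no test to run on them. The between-group analysis would then have to be chosen after the data are in hand, unless another document fixes it.

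**Working it through.** The article gives no effect size, expected rate, SD or power, so there is no planned figure to reproduce. The main check sets the sections side by side.

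**1. Does the named test fit the outcomes in the aim?**

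| Item | What the aim needs (2.1, 2.4, 2.5) | What section 2.6 supplies |
|---|---|---|
| Contrast | Between three randomised groups | Change within each group |
| Data type | Proportions from positive/not-positive or survived/not | Mean and SD |
| Baseline | None described; measured at or after surgery | A change, which needs two time points |
| Number of arms | Three, so three pairwise contrasts | One t-test |

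The two columns disagree in every row. Sensitivity, specificity and accuracy are also ratios for a whole group. Each arm yields one value per outcome, with no SD between patients unless the ratio is computed per patient, which the article does not describe.

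**2. Is there anything the named test could serve?** Yes: the preoperative versus intraoperative measurements in section 2.5, where they are continuous and paired. That analysis describes agreement or shift inside one arm. It is not the aim in section 2.1.

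**3. What if within is a slip for between?** Three arms give three pairs. A single t-test compares only two arms. Three pairwise tests, each at .05, would carry a chance of at least one false positive of about 1 − 0.95³ = 0.143 per outcome. This is an approximation, because the pairs share arms. No adjustment is stated, and the outcomes would still be binary. The mismatch remains in a different form.

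**4. Illustration only: what if arms were compared through separate within-group P values?** Suppose a continuous pre/intraoperative measure changes by the same true amount in all three arms, and let p be the power of each within-group test. The chance that the three verdicts are not all the same is

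1 − p³ − (1 − p)³ = 3p(1 − p).

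With n = 20 per arm and two-sided .05 (the article does not state sidedness), p follows from the noncentral t distribution with 19 degrees of freedom and noncentrality d√20. The standardised changes d are assumed.

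| d | p | Verdicts disagree |
|---|---|---|
| 0 | 0.050 | 14% |
| 0.2 | 0.136 | 35% |
| 0.4 | 0.397 | 72% |
| 0.5 | 0.565 | 74% |
| 0.66 | 0.799 | 48% |
| 0.8 | 0.924 | 21% |
| 1.0 | 0.989 | 3% |

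The maximum is 3 × 0.5 × 0.5 = 75%, at p = 0.5. The answer therefore runs from about 3% to 75% according to an effect size that the article does not give. It cannot apply to the four outcomes in the aim, because they have no within-group change.

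**The case against.** The strongest defence is that the article is condensed. Section 2.5 does announce a comparison of the three methods and a consistency analysis, and naming their tests could fairly be left to an analysis plan. The t-test sentence may simply be meant for the preoperative versus intraoperative measurements, for which it is reasonable. The English is also unreliable in places (for example "when the digital technology can be worn for successful reconstruction is judged to be"), so within may stand for between.

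Part of this stands. Silence on the between-group test would not by itself be a finding, and the t-test has a legitimate use. But section 2.6 is not silent. It states one test without limiting it to those measurements, and that test does not serve the aim. The slip reading does not rescue it either, because a t-test with mean and SD still does not fit three arms and binary outcomes.

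A reader might go further and infer that the randomisation will go unused, or that the arms will be ranked by which of them reaches P < .05 on its own. The documents support neither inference. No section states such a rule, and section 2.5 points to a direct comparison of the methods. For the same reason, no single disagreement rate from the illustration can be presented as this trial's error rate.

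**Conclusion.** The point holds as a mismatch between the stated analysis and the stated aim. The one named test addresses the wrong contrast and the wrong data type for all four outcomes in section 2.1, and the three-way comparison announced in section 2.5 has no test. This conclusion rests on the text alone, needs no assumed effect size, and holds whether within is read literally or as between.

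The 3% to 75% range is a side illustration. It depends on assumed within-group power and on an inferential rule that the article does not state, and it would concern pre/intraoperative measurements only. It shows why the plan should rule out comparing methods through within-group P values. It does not show that the plan does so. The mismatch should be corrected before analysis, because otherwise the stated plan produces no test of the trial's question.

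**What to change.** Rewrite section 2.6 to say:

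1. Flap survival, sensitivity, specificity and accuracy are reported per group as proportions with 95% confidence intervals.
2. For each outcome, the three groups are compared with one overall chi-square test, or Fisher's exact test where expected counts are small.
3. Pairwise differences follow, with confidence intervals and Holm-adjusted P values. CTA + mimics versus CTA is named as the contrast of main interest, with no fixed testing order, since Holm orders contrasts by P value.
4. If several perforators per patient are counted, the analysis allows for clustering within patients.
5. Cochran's Q and McNemar's test are used only if every method is applied to each patient.
6. The within-group t-test is kept for continuous preoperative versus intraoperative measurements only, and within-group P values are not used to compare methods.

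The cost is one paragraph, with no extra data or patients. The change supplies a valid test but not necessarily an informative one. Under assumed rates (the article gives none), a pairwise comparison at 20 per group and two-sided .05 has about 30% power for 80% vs 95% and 35% for 70% vs 90%. At .05/3 = .0167, the strictest Holm step, these fall to 16% and 20%. Reaching 80% power at .05 would take 76 and 62 per group respectively. Across other assumed pairs, power at .05 runs from 9% (90% vs 95%) to 81% (50% vs 90%). Sample size is a separate matter, but the confidence intervals should be given prominence for this reason.

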## Discussion

3

The anterolateral thigh flap has been widely used to repair various tissue defects and has obtained good clinical results. The extensive clinical application mainly focuses on 2 aspects, namely the study of vascular anatomy of lateral flap and the exploration of preoperative flap design technology. Perforator is the direct blood supply source of anterolateral thigh flap, so it is particularly important to study the anatomy of perforator. Therefore, this study will reveal CTA combined with digital technology in the vascular anatomy of the anterior external femoral flap and the design of the flap before and during surgery, so as to provide help for the repair of tissue defects.
